### Intervention Group

The 200 parents randomised to the intervention group will receive a workbook and other resources and weekly scripted telephone contacts of approximately 30 minutes' duration delivered over four weeks. Telephone-based interventions of a similar intensity have previously been found to be effective in adults [43,44]. Each telephone contact aims to provide parents with appropriate knowledge and skills to modify three key domains within the home food environment: availability and accessibility of fruit and vegetables; supportive family eating routines, and parental role-modelling (See Table 1).

**Table 1 T1:** Overview of intervention call content: behaviour change techniques and their application

Key Theme	Content	Behaviour Change Technique	Application of Behaviour Change Technique
**WEEK 1** Availability and Accessibility	Dietary recommendations and serving sizes		
	Children's food diary	Prompt self-monitoring of behaviour	Parents are asked to monitor their children's intake of fruit, and vegetables over 3 days.
	Ways to provide fruit and vegetables throughout the day		
	Setting goals	Prompt specific goal-setting	Parents are encouraged to set a program goal.

**WEEK 2** Availability and Accessibility, Supportive Family Eating Routines	Changing the family routine	Prompt intention formation	Parents decide which activities they will attempt in the coming week.
	Availability and accessibility of foods in the home	Provide general encouragement	Interviewers provide positive feedback about any helpful practices occurring in the home.
	Mealtime practices	Teach to use prompts or cues	Parents learn the HELPS acronym, i.e. try to eat when Hungry, not attempting anything else at the same time (focus on Eating), at an appropriate Location to eat, from a Plate, and while Sitting.
	Meal planning		
	Review of goals	Prompt review of behavioural goals	Parents review the goals they set during the previous calls and evaluate their progress.

**WEEK 3** Parental role-modelling, Supportive Family Eating Routines	The Ps and Cs division of feeding responsibility	Teach to use prompts or cues	Parents learn the Ps and Cs: Parents are encouraged to Plan, Prepare and Provide. Children are encouraged to Choose (whether, what and how much to eat) [49].
	Mealtime strategies to encourage vegetable consumption	Prompt intention formation	Parents decide which activities they will attempt in the coming week.
		Provide general encouragement	Interviewers provide positive feedback about any helpful practices occurring in the home.
	Role-modelling of fruit and vegetable consumption	Prompt identification as a role model	Parents are provided information about their importance in role-modelling fruit and vegetable consumption. Their consumption is compared with national nutrition recommendations. Tailored feedback is provided.

**WEEK 4** Availability and Accessibility Parental role-modelling, Supportive Family Eating Routines	Review of weeks 1-3	Provide general encouragement	Interviewers provide positive feedback about any helpful practices occurring in the home
	Planning for the future and dealing with difficult situations	Prompt barrier identification	Parents are encouraged to identify barriers that will prevent them implementing what they have learnt and to generate solutions.
	Review of goals	Prompt review of behavioural goals	Parents review their program goal, evaluate their progress and identify how they can maintain the change

#### Development and pre-testing of the intervention

The script has been developed by an expert advisory group of clinical and health psychologists, dietitians and health promotion practitioners. The script utilises CATI software [45] to tailor support based on parental report of the home food environment. Intervention development was guided by an existing framework for behavioural therapy development in clinical settings [46]. The pre-testing process involved three phases where the research team piloted preliminary versions of the telephone script and workbook, and refined the intervention based on the feedback received. Each phase of pre-testing was conducted with eight to 12 volunteer health promotion practitioners, parenting experts and parents of young children. Volunteers were asked to comment on content, structure, presentation and length of the intervention, and were encouraged to suggest how the telephone script or workbook could be improved. Feedback from the members of the research team who administered the pre-test telephone calls to volunteers was also sought regarding the ease of administration of the script and the level of volunteer engagement in the intervention.

Following each pre-testing phase, feedback was collated and proposed intervention amendments were discussed by the research team and adopted where feasible. The primary amendments to the intervention telephone script resulting from pre-testing included reducing the length of the calls; changing the order of presentation of intervention content; reducing repetition; providing more examples to clarify key issues; simplifying language; removing jargon; making the script more conversational; and including more opportunities for interaction between parents and interviewers. The primary amendments to the workbook included the addition of more practical information and tools for parents, improving readability through simplifying language, using subheadings and reducing the volume of text, and improvements to the presentation of the workbook to make it more appealing, such as use of bright colours, illustrations and photographs.

#### Intervention content

The telephone intervention script is designed to help parents modify their home food environments through addressing three key domains listed in Table 1. The first column of the table lists each domain at the point at which it appears in the schedule of support calls, while the second column lists the specific topics that are used to explore each of the given domains. Each domain has been associated with increased fruit and vegetable consumption in children as described below.

##### a) Availability and accessibility of fruit and vegetables [10,47]

The telephone intervention encourages parents to ensure that fruit and vegetables are available and accessible in the home and that they are prepared, presented or maintained in a ready-to-eat form that encourages their consumption [48]. This could include offering cut-up pieces of fruit or vegetable at snack times, and ensuring fruit is visible by storing it in fruit bowls.

##### b) Supportive family eating routines

The intervention will seek to improve parent knowledge and facilitate the acquisition of skills to support parents to eat meals as a family [12] without the television on [13], establish and enforce family rules about eating [11] and develop boundaries regarding when and how food is offered to their children [49].

##### c) Parental role-modelling of fruit and vegetable consumption [11]

Parents will be encouraged to increase the number of serves of fruit and vegetables that they consume in front of their children and to express supportive attitudes toward the consumption of fruit and vegetables to their children, for example, by making positive and encouraging comments.

Participants will also be asked to undertake homework activities to encourage them to apply, directly into their home environment, the strategies and information covered in the telephone calls. Incorporating homework assignments into health behaviour interventions has been found to increase the size of the intervention effect [50]. Homework activities will be optional and tailored to the needs of the participant, based on recommended home food environment practices not currently undertaken by the participant.

#### Intervention resources

Based on evidence indicating telephone-based dietary interventions are more effective when used in conjunction with print and other resources [21], all intervention participants will be mailed resource kits following completion of the baseline survey. The kit comprises a participant workbook containing information and activities, a pad of meal planners, and a cookbook including recipes high in fruit and vegetables. The resources will be used to facilitate participant engagement in the telephone support calls and assist participants to complete intervention activities between telephone contacts.

#### Conceptual model

The telephone-based intervention accords with the model of family-based intervention proposed by Golan and colleagues [51] in the treatment and prevention of childhood obesity. Their model, which draws upon socio-ecological theory, focuses on introducing new familial norms associated with healthy eating. This is achieved through making changes within the home food environment, providing positive parental role-modelling and increasing parenting- and nutrition-related knowledge and skills. Interventions based on such a model have been shown to be effective in bringing about environmental changes in participants' homes to support healthy eating [52] and in reducing poor eating habits of overweight and obese children of participants [53].

The intervention utilises a number of specific behaviour change techniques to initiate the change process as describes in Table 1. The third column lists the behaviour change techniques used and the fourth column links each technique to its application in the context of the topic listed in column 2. These behaviour change techniques include prompting intention formation, barrier identification, specific goal-setting and the reviewing of such goals, self-monitoring of behaviour and identification as a role-model, teaching to use prompts or cues, and providing general encouragement, as described in the taxonomy proposed by Abraham and Michie [54].

#### Intervention personnel, recruitment and training

Consistent with other telephone-based health behavioural interventions [20,21], intervention support will be delivered by trained telephone interviewers. Interviewers delivering the intervention will have experience in conducting health-related telephone surveys, but have no formal qualifications in psychology, dietetics, parenting, health promotion or other health professions. The use of telephone interviewers without specialist skills may mean that adoption of this intervention by government agencies is more feasible. Interviewers without specialist skills have previously been found to be effective in improving other health behaviours [20]. If effective in this context, their use may facilitate the adoption of this type of intervention where use of specialist staff may not be feasible due to cost and the shortage of staff with such skills.

To recruit suitable staff and to equip them with the necessary knowledge and skills to deliver the intervention, a pool of potential telephone interviewers was invited to attend a two-day training workshop. The training was developed and delivered by a registered dietitian, a clinical psychologist specialising in parenting, and health promotion practitioners (with post-graduate qualifications and experience in public health). The research team and clinical psychologist judged interviewer competency, based on the completion of role-plays [55] and small group exercises during training, and those considered sufficiently competent were selected to deliver the intervention. The selected interviewers were then required to complete a further minimum 10 hours of self-paced practice, including script and workbook familiarisation. They were also required to practise each script with a member of the research team to ensure that required levels of competency and adherence had been met [55] and that they were able to deliver the script in a confident, conversational style and respond appropriately to participant queries.

During the first two months of intervention delivery, all interviewers will participate in fortnightly group supervision, facilitated by a psychologist. A self-regulatory model of peer supervision [56] will be utilised to facilitate learning, improve interviewer performance and help standardise intervention delivery. Members of the research team will monitor the supervision sessions and provide feedback as required.

#### Intervention monitoring

To ensure integrity of intervention delivery during the trial, members of the research team will have weekly contact with interviewers to keep abreast of common issues and concerns so that they may be addressed in a consistent manner. During each four-week batch of telephone calls, members of the research team will monitor at least two completed calls made by each interviewer to assess adherence with the intervention protocol. Specifically, the research team member will record whether the interviewer covers the key themes and information for each call, the extent to which the interviewer deviates from the script, the length of the call and whether the interviewer adequately answers any questions asked.

The records of the recruitment coordinator will be audited following the recruitment of each batch of participants. A separate member of the research team will review the dates on which allocation letters are mailed. They will also review the attempt dates, receipt dates and completion dates of intervention and data collection telephone calls for each trial participant. This periodic review of documentation will assess whether the intervention is progressing in a timely manner and in accordance with the study protocol [57].

### Control Group

Participants allocated to the control group will receive a 22-page booklet, 'The Australian Guide to Healthy Eating: Background information for consumers' [28]. This is a national food guide published by the Australian Government Department of Health and Ageing. This publication will be posted to parents' residential addresses following completion of the baseline survey.

### Data Collection and Measures

Baseline and follow-up data will be collected through a CATI survey administered to all participants. The survey will take approximately 30 minutes to complete. Data collection interviewers will be provided with training to ensure that they understand and adhere to data collection protocols, and to practise the survey script.

Baseline data will be collected one to two weeks prior to intervention delivery. Calls will be monitored for adherence to the training protocol. Members of the research team will monitor approximately ten percent of the first batch of baseline calls and compare the delivery of the survey to the script as written. Any deviations from the protocol will be addressed with the interviewer immediately following the completion of the call. Each interviewer will then be monitored at least once in each subsequent batch of surveys to ensure consistency over time. The survey administered at baseline will be repeated at four time points: two, six, 12 and 18 months following baseline data collection. To minimise attrition, prior to follow-up data collection calls at six, 12 and 18 months, participants will receive letters thanking them for their participation to date and reminding them that they will shortly be telephoned to participate in follow-up phone calls [58].

Data collection interviewers will not participate in trial recruitment or intervention delivery and will be blind to participant group allocation. Furthermore, during each follow-up data collection interview, participants will be asked not to disclose their group allocation to the interviewers at the start of the telephone survey. To assess the effectiveness of the blinding, following the collection of trial outcome data, interviewers will be asked to nominate the groups to which they believe the participants were allocated [59].

### Measures

#### Demographics

Demographic items regarding parents' gender, age, Aboriginal and/or Torres Strait Islander status, education, income, postcode and household composition (e.g. the number of children in the household), as well as questions regarding the child's gender and age, will be assessed at baseline. Items used to assess demographics will be sourced from the NSW Health Survey Program, a regular government behavioural risk factor surveillance survey [60].

#### Process measures

The CATI system will record information regarding the outcome of each attempted call (e.g. engaged, answering machine, call-back arranged, call partially complete, call complete or refusal), the interviewer who attempted the call, the date and time of the attempt, the call duration and the responses provided by the participant throughout the call. During intervention delivery calls, participants will be asked whether they received the intervention resources and what homework activities they attempted. This will allow for an assessment of the extent to which the intervention was delivered and received as planned.

#### Primary outcome measure: fruit and vegetable consumption

The primary outcome is the change in the fruit and vegetable intake of the preschool children. Fruit and vegetable intake will be assessed using the fruit and vegetable subscale of the Children's Dietary Questionnaire. This questionnaire was developed to assess Australian children's dietary patterns in relation to current national guidelines and has been recommended for use in assessing the efficacy of interventions to improve children's eating habits [61].

This semi-quantitative food frequency questionnaire asks parents to report the frequency and variety of foods consumed by their children over the previous seven days and the previous 24 hours. Scores on the fruit and vegetable subscale range from 0 to 28, with a score of 14 recommended based on current national dietary guidelines [61]. A one-point increase on this subscale could equate to, for example, a child consuming on average an additional type of fruit or vegetable each day (variety), or consuming fruit or vegetables at an additional eating occasion each day (frequency). An increase of this magnitude of fruit and vegetable variety or frequency of consumption is consistent with effect sizes of fruit and vegetable consumption reported in previous child fruit and vegetable interventions, and has the potential to have significant public health impact [62]. Reliability and validity of this tool has been established using multiple samples of Australian children, including preschoolers [61]. The fruit and vegetable subscale was found to be internally consistent (∝ = 0.76), reliable (intra-class correlation coefficient = 0.75) and valid as assessed against a seven-day food checklist (Spearman's correlation coefficient = 0.58) [61].

#### Sample size

A sample size of approximately 300 participants (150 per group) at the 18-month follow-up will allow a detectable difference between intervention and control groups of 1.27 on the fruit and vegetable subscale of the Children's Dietary Questionnaire, with 80% power at the 0.05 significance level. This sample size accounts for the effect of clustering by assuming an interclass correlation coefficient of 0.03 (unpublished data from the *Good for Kids *program) and assumes 10 participants per preschool remain at the 18-month follow-up (as explained below).

Four hundred participants will be required to be recruited at baseline to achieve the desired sample of 300 at the 18 month follow-up. Based on preschools caring for an average of 27 children each day [34], and assuming children attend preschool for an average of 2.8 days per week (i.e. 17 hours over 6-hour long days), it is expected that up to 48 parents of children, on average, will be eligible to participate in the trial from each consenting preschool. A parent participation rate of 30% [19] will yield approximately 14 parents per preschool at baseline, of whom 10 will remain at 18 months, assuming a 25% attrition rate [63]. It is thus estimated that 30 preschools will be required to generate a sample of 300 parents at the conclusion of the trial.

#### Statistical analysis: primary outcome

All statistical analyses will be performed with SAS (version 9.2 or later) statistical software.

To assess the initial impact of the intervention and the extent to which any intervention effect is maintained in the longer term, the primary outcome analyses for the trial will be conducted on participant scores on the fruit and vegetable subscale of the Children's Dietary Questionnaire collected at the two-month and 18-month follow-up time periods. For the primary outcome analyses, an alpha value of 0.05 will be utilised to determine statistical significance.

Outcome data will be analysed using general estimating equations based on the intention-to-treat principle, where participants are analysed based on the groups to which they were allocated, regardless of the treatment type or exposure that they actually received [64]. General estimating equation models will account for any clustering effect of preschools. To ensure the results of the primary analysis are robust against the missing data assumption of the general estimating equation, a sensitivity analysis will be performed whereby participants' observations at baseline will be used as a substitute for subsequent missing data. A per-protocol analysis will also be conducted whereby outcome data will only be included in analyses if participants received and completed all four telephone support calls. Conducting both intention-to-treat and per-protocol analyses is recommended when assessing trial outcomes [64].

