**Methods/Design:**

The study, conducted in the Hunter region of New South Wales, Australia, employs a cluster randomised controlled trial design. Two hundred parents from 15 randomly selected preschools will be randomised to receive the intervention, which consists of print resources and four weekly 30-minute telephone support calls delivered by trained telephone interviewers. The calls will assist parents to increase the availability and accessibility of fruit and vegetables in the home, create supportive family eating routines and role-model fruit and vegetable consumption. A further two hundred parents will be randomly allocated to the control group and will receive printed nutrition information only. The primary outcome of the trial will be the change in the child's consumption of fruit and vegetables as measured by the fruit and vegetable subscale of the Children's Dietary Questionnaire. Pre-intervention and post-intervention parent surveys will be administered over the telephone. Baseline surveys will occur one to two weeks prior to intervention delivery, with follow-up data collection calls occurring two, six, 12 and 18 months following baseline data collection.

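### The primary outcome is defined as change but the primary analysis is worded on follow-up scores, and the article does not say how the baseline score enters the model

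*Protocol article*

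**What the plan says.** Two places define the outcome as a change. The Abstract (Methods/Design) has "The primary outcome of the trial will be the change in the child's consumption of fruit and vegetables", and the section on the primary outcome measure has "The primary outcome is the change in the fruit and vegetable intake of the preschool children".

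The section on the statistical analysis of the primary outcome describes the analysis variable differently: "the primary outcome analyses for the trial will be conducted on participant scores on the fruit and vegetable subscale", with the data "collected at the two-month and 18-month follow-up time periods". Baseline is not among the time points listed. The one feature of the model that is described is the handling of preschools: "General estimating equation models will account for any clustering effect of preschools". Baseline scores appear once in that section, in a sensitivity analysis where "participants' observations at baseline will be used as a substitute for subsequent missing data".

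The baseline score will be available. The Data Collection section states: "The survey administered at baseline will be repeated at four time points".

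**The concern.** The article names one quantity as the outcome and another as the thing analysed, and no sentence connects them. A statistician working from this text could defensibly fit any of these:

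- the follow-up score compared between arms;
- the change from baseline compared between arms;
- the follow-up score compared between arms with baseline as a covariate (or a repeated-measures model with a group-by-time term).

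On the same data these give different estimates, standard errors and p-values, so the text does not fix one primary analysis. The choice also affects precision. Two readings follow the words most literally: raw change from the outcome definition, and follow-up scores from the analysis section. In large samples neither is more precise than the baseline-adjusted comparison, and the data for that comparison are already being collected.

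**Working it through.** **Inputs from the Sample size section:** 150 per group at 18 months, detectable difference 1.27, 80% power, significance level 0.05 (taken as two-sided), intraclass correlation 0.03, 10 participants per preschool.

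**Not in the documents:** the standard deviation (SD), whether 1.27 refers to scores, changes or adjusted scores, and the correlation r between baseline and follow-up.

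**Step 1: the plan's own figure.** Without an SD the 300 cannot be reproduced independently, but the SD it implies can be solved for.

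- Design effect = 1 + (10 − 1) × 0.03 = 1.27 (equal to the detectable difference by coincidence).
- Effective n per arm = 150 / 1.27 = 118.1.
- Implied SD = 1.27 / [(1.960 + 0.842) × √(2/118.1)] = 3.48.
- Implied standard error of the difference = 1.27 / 2.802 = 0.453.
- Recruitment: 300 / (1 − 0.25) = 400, as stated.

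The figures are consistent with one another. They do not show which variable the SD belongs to, so the sample size does not settle how baseline is used.

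**Step 2: do the three analyses target the same effect?** Yes. Randomisation makes the expected baseline difference zero, so the expected between-arm difference in follow-up score equals that in change. With baseline as a covariate in a linear model the arm coefficient is identical for either dependent variable, because subtracting baseline from the left side only shifts the baseline coefficient by one.

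**Step 3: relative precision.** With equal variances at baseline and follow-up, the variance factors relative to the follow-up score are 1 (follow-up), 2(1 − r) (change) and 1 − r² (baseline-adjusted).

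- Change is worse than follow-up when 2(1 − r) > 1, that is when r < 0.5.
- Adjusted is never worse than follow-up, since 1 − r² ≤ 1.
- Adjusted is never worse than change, since 2(1 − r) − (1 − r²) = (1 − r)² ≥ 0.

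**Step 4: size over a range of r.** This assumes that 1.27 belongs to the unadjusted follow-up score and that each factor applies to the whole variance, between and within preschools. Detectable difference = 1.27 × √factor. Power is for a true difference of 1.27.

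| r | Follow-up score | Change score | Baseline-adjusted |
|---|---|---|---|
| 0.3 | 1.27 (80%) | 1.50 (65.8%) | 1.21 (83.6%) |
| 0.5 | 1.27 (80%) | 1.27 (80.0%) | 1.10 (89.9%) |
| 0.7 | 1.27 (80%) | 0.98 (95.1%) | 0.91 (97.5%) |

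For the one-point increase that the outcome section discusses, power is Φ(1/0.453 − 1.96) = 60% for the follow-up score. At r = 0.5 the adjusted standard error is 0.453 × √0.75 = 0.392 and power is 72%.

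The outcome section calls the subscale "reliable (intra-class correlation coefficient = 0.75"). That figure comes from validation samples and is not the correlation over 18 months. It is at most a rough upper guide to r.

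**The case against.** The strongest reply is that the article lists no terms of the mean model at all, so silence about baseline is not exclusion. Covariates are commonly left to a full protocol or analysis plan, which is not shown. This stands: a reader might infer that the primary model has no baseline term, but the text does not say so.

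A reader might also infer that the two sections contradict each other on the effect being estimated. Step 2 of the working shows that they do not. Change can be read as the concept and the scores as its measurement, and filling missing follow-up values with baseline amounts to assuming zero change, which sits comfortably with a change analysis.

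A third inference is that chance baseline imbalance between only 30 preschools would pass straight into an unadjusted result. The expected carry-over is about r times the imbalance, and that variation is already inside the unadjusted standard error. It is not bias and does not inflate the type I error. Allocation is also blocked and stratified by area socio-economic status, and the assumed intraclass correlation is small.

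Lastly, the gains in the table depend on an r that the documents do not give and on 1.27 being an unadjusted figure. If its SD came from changes or adjusted scores, those gains do not follow.

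What the reply does not remove is that the article itself attaches two different variables to its primary outcome and leaves the link unstated.

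**Conclusion.** The point holds as an unreconciled analysis variable with a free gain in precision available. Follow-up, change-score and baseline-adjusted analyses all fit the text and share the same expected effect. The baseline-adjusted one is at least as precise as the others in large samples, and raw change is the least precise of the three if r is below 0.5.

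Under the two assumptions of Step 4, adjustment would bring the detectable difference from 1.27 to between about 1.21 and 0.91 for r from 0.3 to 0.7. This is an illustration over an assumed range, not a measured loss.

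The documents do not support concluding that the stated sample size is wrong, that baseline is definitely left out, or that an unadjusted analysis would be biased. A clustered comparison of follow-up scores would be valid. The matter is worth correcting because the choice should be fixed in advance, not because a result would otherwise be invalid.

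**What to change.** Name one primary analysis and word the Abstract, the primary outcome section and the analysis section to match it. At each of the two primary time points, compare the child's follow-up subscale score between arms in the preschool-clustered estimating-equation model, with the child's baseline subscale score as a covariate. Report the result as a baseline-adjusted mean difference.

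The word change may stay as a description of the aim, provided that the text says it is estimated in this way.

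The cost is one sentence in the analysis section and matching wording in the other two places. No extra data are needed. The baseline survey goes to all participants and parents are told their allocation only after it, so the baseline score is a sound covariate. Sample size and recruitment need not change.
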